### **Secondary efficacy endpoints**

All analyses of secondary efficacy endpoints will be performed by appropriate descriptive statistics.

The value of CD86+pDC /  $10^5$  lymphocytes at Screening Visit as a predictor of RFS will be tested within a Cox model. As treatment group (A or B) is assumed to be associated with RFS, for validation, the Cox model will be stratified for treatment group to remove its influence. However, to also judge the prognostic value of CD86+pDC additional to treatment group, treatment group and a possible interaction term between both factors will be considered together in an unstratified Cox model.

Apart from attempting validation of the prognostic influence for CD86+pDC /  $10^5$  lymphocytes, the prognostic influence of further clinical, immunological, and genetic biomarkers on relapse-free survival is investigated. To perform these explorative analyses, candidate variables are considered as part of a multivariate Cox model stratified for treatment.

For overall survival the same analyses as for RFS over time will be performed. Whether multivariate analyses are possible depends on the number of events.

All secondary endpoints will be evaluated at the final analysis which is performed after the 25-month follow-up for all randomized patients was collected.

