**Secondary Objectives:**

To assess tolerability and toxicity of AOP2014

To assess quality of life before and after TKI discontinuation

To evaluate the safety of maintenance therapy with AOP2014

To assess overall survival

To explore the value of 95 CD86+pDC /  $10^5$  lymphocytes at baseline in predicting risk of molecular relapse (loss of MMR)

Explore immunological and genetic biomarkers to study biology of TFR, and identify predictors IFN response (e.g. mRNA sequencing of whole blood or leukocyte subpopulations, PD-L1-, PD1-, CD62L- measurements by FACS on peripheral blood subsets, T-cell activation and exhaustion marker measurements, PR1-CTL assessment and cytokines). Evaluation of cytokines/chemokines (i.e., IL-6, IFN- $\alpha$ , IL 10, and others).

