### 4.2 Secondary endpoints

- RFS 13 months after randomization
- RFS 25 months after randomization
- Safety, tolerability and toxicity based on incidences of adverse events, serious adverse events, frequency of clinical laboratory tests by worst toxicity grade
- Quality of life (EORTC QLQ-C30 and EORTC-QLQ-CML24 questionnaires) The QoL assessment in this study is planned to gain information on the QoL of CML patients under stopping conditions. The data will be compared between the treatment groups and to QoL of normal population. Furthermore, results of the CML24 module should be shared with the EORTC group to complete the validation of this questionnaire
- Explore the value of  $95 \text{ CD86+ pDC} / 10^5$  lymphocytes at baseline (before TKI stop) as a predictor of TFR
- Overall survival (OS), defined as the time between the date of randomization and the date of death from any cause.
- Explore immunological and genetic biomarkers to study biology of TFR, and identify predictors IFN response (e.g. mRNA sequencing of whole blood or leukocyte subpopulations, PD-L1-, PD1-, CD62L- measurements by FACS on peripheral blood subsets, T-cell activation and exhaustion marker measurements, PR1-CTL assessment and cytokines).
- Evaluation of cytokines/chemokines (i.e., IL-6, IFN- $\alpha$ , IL 10, and others).
- Kinetics of BCR-ABL transcript level over time after TKI stop

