Finally, cells from the peripheral blood will be analyzed to assess whether the response to IFN and/or IFN-typical adverse events (depression, autoimmune phenomena) can be predicted from biomarkers measured before and initiation of IFN treatment and during treatment. Such predictive potential has

been demonstrated in patients with hepatitis C or malignant melanoma, who were treated with IFN. For these studies, EDTA blood (9 to 10 ml) from the peripheral blood will be used and subjected to nucleic acid (RNA, DNA) and signal transduction (protein) analyses in the laboratory of [name] at the University Hospital of Aachen (see Study Personnel and Table 1 and Table 2). Samples will be taken before and during IFN therapy from patients in the Arm A and also those in the comparator Arm B (to control for IFN effects).

The patient can participate in the study without donating blood for those accompanying translational projects. The biomaterial sampled during this study cannot be used for commercial purpose.

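### For biomarkers other than CD86+pDC, section 16.7 states only a prognostic Cox model stratified by arm, which cannot identify predictors of IFN response, a declared objective

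*Protocol*

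**What the plan says.** The protocol states the aim in section 4.2: "Explore immunological and genetic biomarkers to study biology of TFR, and identify predictors IFN response". The synopsis repeats it under objectives and endpoints, and section 3.2 states it again. Section 12.2.11 adds that the laboratory work asks whether response to interferon, or its typical adverse events, "can be predicted from biomarkers measured before and initiation of IFN treatment and during treatment". Samples come from "patients in the Arm A and also those in the comparator Arm B (to control for IFN effects").

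CD86+pDC has a separate objective, the value of its count per 100,000 "lymphocytes at baseline in predicting risk of molecular relapse (loss of MMR").

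Under Secondary efficacy endpoints, section 16.7 gives two analyses:

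- **CD86+pDC:** a Cox model stratified by arm, and in addition "treatment group and a possible interaction term between both factors will be considered together in an unstratified Cox model".
- **All other markers:** "the prognostic influence of further clinical, immunological, and genetic biomarkers on relapse-free survival is investigated". The method is that "candidate variables are considered as part of a multivariate Cox model stratified for treatment". No interaction is mentioned.

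**The concern.** Stratifying a Cox model by arm lets the baseline hazard differ between arms but estimates one log hazard ratio per marker, common to both. That quantity says who relapses. A predictor of interferon response is a marker whose hazard ratio differs between arms, and that difference is not a parameter of the stated model.

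The plan already contains the suitable model but gives it only to CD86+pDC, whose objective is relapse risk. The markers tied to the interferon-response objective do not get it. As written, the stated analysis leaves that part of the objective unanswered, although the design collects marker data in both arms.

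**Working it through.** **1. The plan's own figures.** Section 16.10 assumes 25-month RFS of 45% in arm B and 65% in arm A, two-sided 0.05 and 80% power.

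n per arm = [1.96·√(2·0.55·0.45) + 0.8416·√(0.45·0.55 + 0.65·0.35)]² / 0.20² = (1.379 + 0.580)² / 0.04 = 95.9, so 96 per arm and 192 in all. With 10% drop-out, 192/0.9 = 213.3, so 214. Power with 96 per arm is 83.3%, 81.3% and 80.0% at 7, 13 and 25 months. These agree with the protocol and are not in dispute; they only set the event count.

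**2. Expected events by 25 months.** Arm A: 96 × 0.35 = 33.6. Arm B: 96 × 0.55 = 52.8. Total: 86.4.

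**3. Approximate power.** Assume a binary marker with 50% prevalence; the protocol gives neither prevalence nor effect size. The information per arm is events × 0.5 × 0.5, so I_A = 8.4 and I_B = 13.2. Let b_A and b_B be the log hazard ratios of the marker in each arm.

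- Stated model: common effect = (I_A·b_A + I_B·b_B)/(I_A + I_B), SE = 1/√21.6 = 0.215.
- Interaction: b_A − b_B, SE = √(1/8.4 + 1/13.2) = 0.441.
- Power ≈ Φ(|effect|/SE − 1.96) + Φ(−|effect|/SE − 1.96).

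*Marker acting only under AOP2014 (HR 0.5 in A, 1.0 in B).* Common effect = 8.4 × (−0.693)/21.6 = −0.270, HR 0.76, z = 1.25, power 24%. Interaction: z = 0.693/0.441 = 1.57, power 35%.

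*Purely prognostic marker (HR 0.5 in both arms).* Common effect: z = 0.693/0.215 = 3.22, power 90%. Interaction: 5%, as it should be.

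*Opposite effects (HR 0.5 in A, 1.55 in B).* Common effect = 0, so 5%. Interaction: z = (0.693 + 0.441)/0.441 = 2.57, power 73%.

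**4. Check by simulation.** Exponential times, 96 per arm, censoring at 25 months, 300 trials per scenario:

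| Assumed marker | Stated model | Interaction term |
|---|---|---|
| Effect in arm A only | 20% (mean common HR 0.77) | 31% |
| Prognostic only | 89% | 4% |
| Opposite effects | 5% | 71% |

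A second simulation used a standard-normal marker with HR 0.67 per SD and 500 trials per scenario. It gave 28% and 44% for an effect in arm A only, 96% and 5% for a prognostic marker, and 5% and 82% for opposite effects (0.67 in A, 1.25 in B). The pattern is the same.

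**5. Optional sampling.** Steps 3 and 4 give all 192 patients marker data, but sections 12.2.11 and 19.3 make translational sampling voluntary. If a share f takes part, z shrinks by √f. For the binary marker acting only in arm A, interaction power falls from 35% to 26% at f = 0.7 (z = 1.31) and to 20% at f = 0.5 (z = 1.11). Both shares are assumptions.

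**6. Other places that might supply the term.** Section 16.4 lists correlation of outcome with predefined biomarkers without a comparison of arms. The explorative logistic and Cox regressions under the primary endpoint in 16.7 concern the influence of baseline covariates. Neither contains a marker-by-arm term.

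**The case against.** The strongest reply is that the criticised sentence does what it claims. It announces prognostic influence, and a model stratified by arm is a correct tool for that. It also serves the other half of the objective, the biology of treatment-free remission. On this view the plan merely leaves the model for predictors of response to the SAP. The first part stands: the model suits its stated target and should stay. The second does not remove the point. The protocol is not silent on these markers; it fixes a target and a model for them, and neither matches the declared aim, while the neighbouring sentences do provide an interaction for another marker.

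It can also be said that response to interferon need not mean a difference in RFS benefit. Section 12.2.11 speaks of in-vitro response, of adverse events and of markers measured during treatment. Sampling arm B may simply control for marker changes that interferon induces, so it does not prove that a marker-by-arm analysis of RFS was intended. This is fair. The point is therefore limited to response in terms of RFS and to baseline markers.

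Stratification does not technically forbid a marker-by-arm term. But none is stated for these markers, although one is stated for CD86+pDC.

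Three stronger readings are tempting and not supported:

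- That the whole biomarker analysis lacks an interaction. It does not, because CD86+pDC has one.
- That the stated model misses predictive markers altogether. An effect confined to arm A can surface as a weak common effect; what is lost is the ability to recognise it as predictive.
- That prognostic markers will be reported as predictors of response. The section labels its result prognostic, so this is only a risk if the result is later presented under the objective.

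**Conclusion.** The point holds for biomarkers other than CD86+pDC: the stated analysis cannot identify any of them as predictive of interferon response on RFS.

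The realistic size is modest. For an effect confined to arm A, the stated model is significant in about 20–30% of trials across the two marker types, with nothing to separate the result from weak prognosis. The interaction term is significant in roughly 30–45%, and in fewer where patients decline translational sampling. The striking contrast (5% against 71–82%) needs a marker effect that reverses between arms, which nothing in the protocol supports; it shows what can happen, not what to expect. All these figures rest on assumed marker prevalence and hazard ratios.

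The analyses are explorative under sections 16.7 and 16.11. The four confirmatory hypotheses and the sample size are untouched. The change is worth making because an explorative analysis should still estimate the quantity named in its objective.

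**What to change.** In section 16.7, keep the stratified Cox model for prognostic influence. For predictors of interferon response on RFS, add for candidate baseline markers the model already planned for CD86+pDC: marker, arm and marker-by-arm interaction. Report the interaction estimate and the arm-specific hazard ratios with 95% confidence intervals, labelled explorative. The candidates include sequencing, flow cytometry and cytokine data, so account for multiplicity, for example by false discovery rate, and do not declare predictors on separate 0.05 tests. State how many patients contributed samples. If this analysis is not wanted, restate the objective and endpoint as prognostic in the synopsis and in sections 3.2 and 4.2.

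The cost is a few extra explorative models on data already being collected, and interaction estimates that will be imprecise. No added patients or samples are needed. Predictors of adverse events and markers measured on treatment, also mentioned in section 12.2.11, are outside this change.

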### **Safety endpoints**

The safety analyses will be based on the safety population. Safety variables will be tabulated by treatment group and listings will be given.

Cumulative probabilities of the occurrence of adverse events will be calculated. Firstly, cumulative probabilities for the occurrence of any adverse event, secondly the occurrence of any adverse event of grade 3 or 4 will be plotted by cumulative incidence curves. Cumulative incidence curves will consider competing risks. One competing risk would be death without prior recording of any adverse event.

Using cumulative incidence curves, also probabilities for the observation of particular adverse events of interest are considered.

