| Skin and subcutaneous tissue disorder                | common : pruritus, alopecia, rash, erythema, psoriasis, xeroderma, dermatitis acneiform, hyperkeratosis, hyperhidrosis
uncommon : photosensitivity reaction, skin exfoliation, nail dystrophy, dry skin                                                                    |
| Musculoskeletal and connective tissue disorders      | very common : arthralgia, myalgia
common : arthritis, pain in extremity, musculoskeletal pain, bone pain, muscle spasms
uncommon : sjogren's syndrome, muscular weakness, neck pain, groin pain                                                                  |
| Renal and urinary disorders                          | uncommon : cystitis haemorrhagic, dysuria, micturition urgency, urinary retention                                                                                                                                                                                                    |
| Reproductive system and breast disorders             | uncommon : erectile dysfunction                                                                                                                                                                                                                                                      |
| General disorders and administration site conditions | very common : influenza like illness, fatigue
common : pyrexia, injection site reaction, asthenia, chills, general physical health deterioration, injection site erythema
uncommon : injection site pain, injection site pruritus, sensitivity to weather change |
| Investigations                                       | common : anti-thyroid antibody positive, blood thyroid stimulating hormone increased, body temperature increased, antinuclear antibody positive
uncommon : blood uric acid increased, blood lactate dehydrogenase increased, coombs test positive, weight decreased        |

Adverse events related to AOP2014 treatment (as listed in **IB Version 10.1, 21 March 2017, Table 5-12**)

Furthermore the Notification to investigators was published (dated 11 August 2017), listing the following new adverse events with possible relation:

- · Acute myocardial infarction
- · Urinary tract infection
- · Suicide

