#### **14.1.4 Serious Adverse Event (SAE) or Serious Adverse Reaction (SAR)**

A serious adverse event or serious adverse reaction is defined as follows:

'Any untoward medical occurrence or effect that at any dose:

- results in death,
- is life-threatening,
- requires hospitalization or prolongation of existing hospitalization,
- results in persistent or significant disability or incapacity,
- or is a congenital anomaly or birth defect'.

'NOTE: The term "life-threatening" in the definition of "serious" refers to an event in which the patient was at risk of death at the time of the event; it does not refer to an event which hypothetically might have caused death if it were more severe'.

The severity of an adverse reaction is largely determined by the outcome of the medical occurrence. An adverse reaction should only be termed "serious" if hospitalization did in fact take place as a result of it. As a rule, hospitalization is the admission to a hospital with at least one overnight stay.

The presentation of a patient in the emergency room (casualty center, health care center) alone without subsequent in-patient admission does not yet fulfill the criterion hospitalization. However, it should be proofed whether any of the other criteria mentioned above justifies an adverse reaction being classified as "serious" or at least "medically significant".

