### 14.3 Severity

Severity of AEs will be graded according to the 'National Cancer Institute - Common Terminology Criteria for Adverse Events' (CTCAE – Version-No.4.0).

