## 16.6 Safety Variables

The following safety assessments are considered as safety endpoints:

- Safety profile of AOP2014 in terms of the incidence of AEs graded according to NCI CTC Version 4.03;
- Autoimmunity induced by AOP2014 in terms of ANA.

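### The severe-AE incidence curve is defined on grade 3 or 4 only, so a patient whose only severe AE is fatal and recorded at grade 5 is not an event on it

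*Protocol*

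**What the plan says.** Protocol section 16.7, under Safety endpoints, plans two curves in the safety population.

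- First curve: "Firstly, cumulative probabilities for the occurrence of any adverse event".
- Second curve: "secondly the occurrence of any adverse event of grade 3 or 4 will be plotted by cumulative incidence curves".

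On competing risks it makes one general statement, "Cumulative incidence curves will consider competing risks", and gives one example: "One competing risk would be death without prior recording of any adverse event". It gives no separate competing risk for the second curve.

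Three other places bear on the point.

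- Grading. Section 14.3 states: "Severity of AEs will be graded according to the 'National Cancer Institute - Common Terminology Criteria for Adverse Events". The safety endpoint in section 16.6 is "Safety profile of AOP2014 in terms of the incidence of AEs graded according to NCI CTC Version 4.03", with no upper limit on grade.
- Fatal events are foreseen. "results in death" is the first seriousness criterion in section 14.1.4, and section 14.4.2 lists fatal among the AE outcomes.
- Section 10.2 reports a recent safety notice: "Furthermore the Notification to investigators was published (dated 11 August 2017), listing the following new adverse events with possible relation". The events listed are acute myocardial infarction, urinary tract infection and suicide.

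**The concern.** The second curve is the planned picture of severe toxicity over time. Its event definition stops one grade below the worst outcome, and nothing elsewhere in the protocol extends it to fatal events.

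The example of a competing risk does not fill the gap. It requires that no AE of any grade was recorded before the death. That is the right condition for the any-AE curve. For the severe-AE curve it is too narrow, above all in arm A: section 7 expects flu-like effects as a matter of routine, and section 10.2 lists influenza-like illness and fatigue as very common. Most arm A patients will probably have a low-grade AE on record early.

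The protocol's own safety information supplies a concrete case. Depression is listed as common and suicide as newly notified with possible relation. A patient with grade 2 depression who then dies by suicide, recorded at grade 5, would not be an event on the severe-AE curve and would not meet the competing risk that is named.

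**Working it through.** The protocol states no figure for this curve, so there is none to reproduce. The check has two parts.

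**1. What the wording does with each kind of patient.** The protocol does not print the grading scale. That grade 5 means a fatal AE comes from CTCAE, which sections 14.3 and 16.6 adopt.

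| Patient | Event on the grade 3 or 4 curve? | Named competing risk? |
|---|---|---|
| Earlier separate grade 3 or 4 AE, then a fatal AE | Yes, at the earlier AE | Not needed |
| Fatal AE first recorded at grade 3 or 4 | Yes | Not needed |
| Earlier grade 1 or 2 AE, then an AE recorded only at grade 5 | No | No, an AE was already recorded |
| No earlier AE, sudden fatal AE at grade 5 | No | Arguable: depends on whether the fatal AE itself counts as a prior record |
| Earlier grade 1 or 2 AE, then a death not recorded as an AE | No, and rightly so | No, an AE was already recorded |

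Rows three and four show the gap in the event definition. Rows three and five show the gap in the example of a competing risk.

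**2. Size on the curve.** Arm size: 214 randomized 1:1 gives 214/2 = 107 per arm. The safety population may be slightly smaller. The protocol gives no expected counts, so the following are assumptions: *g* = 20 or 30 patients with a first grade 3 or 4 AE; *d* = 1, 2 or 4 patients whose only severe AE is fatal, each after a grade 1 or 2 AE; event times uniform over 15 months; no other losses. Three ways of handling the *d* deaths are compared at 15 months:

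- event is grade 3 or higher: (*g* + *d*)/107
- death is a competing risk: *g*/107
- death is censored: Aalen-Johansen estimate with the death treated as a loss to follow-up, averaged over 400 simulated arms

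| *g* | *d* | Grade 3 or higher | Competing risk | Censored |
|---|---|---|---|---|
| 20 | 1 | 19.63% | 18.69% | 18.79% |
| 20 | 2 | 20.56% | 18.69% | 18.88% |
| 20 | 4 | 22.43% | 18.69% | 19.08% |
| 30 | 1 | 28.97% | 28.04% | 28.18% |
| 30 | 2 | 29.90% | 28.04% | 28.32% |
| 30 | 4 | 31.78% | 28.04% | 28.62% |

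Understatement per death, against the curve for grade 3 or higher:

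- As a competing risk: 1/107 = 0.93 points in every row.
- As censored, *g* = 20: 19.63 − 18.79 = 0.84; (22.43 − 19.08)/4 = 0.84.
- As censored, *g* = 30: 28.97 − 28.18 = 0.79; (31.78 − 28.62)/4 = 0.79.

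So the loss is about 0.8 to 0.9 points per death, whichever way such deaths are handled. As a check on the simulation with one death, the censored estimate must lie between *g*/107 (death at the end) and *g*/106 (death at the start). That is 18.69% to 18.87% for *g* = 20 and 28.04% to 28.30% for *g* = 30, and it does.

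**The case against.** The strongest reply is that competing risks are left open. The text says that they will be considered and then offers one by way of illustration. The natural counterpart for the second curve is death without an earlier grade 3 or 4 AE, and listing competing risks curve by curve is ordinary content of a statistical analysis plan. Section 16.7 also discusses, for relapse, when censoring is unsuitable and a competing-risk estimate is needed, so the authors know the difference. This stands. A reader might infer that deaths after a mild AE will be censored as though the patient were still at risk. The protocol does not say so; it only leaves the handling unstated. It does not rescue the event definition, though: with death as a competing risk, a fatal AE still does not count as a severe AE.

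A reader might also infer that every fatal AE is lost from the curve. That goes too far. A patient with any earlier grade 3 or 4 record is already an event, and a sudden death with no earlier AE can be read as the competing risk that is named.

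Nor do fatal AEs disappear from the trial's reporting. They enter the SAE incidence (section 4.2), AE incidence by grade (section 16.6), the tables and listings by arm (section 16.7), overall survival, and the any-AE curve if the fatal AE is the first one. That stands too, and it limits the point to one plot.

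Finally, a grade 3 or 4 curve with death as a competing risk is a coherent summary of non-fatal severe toxicity. But section 16.7 does not describe it as such.

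**Conclusion.** The point holds for the event definition: as worded, the severe-AE curve omits grade 5, and a patient whose only severe AE is fatal and recorded at that grade, with no earlier grade 3 or 4 record, is not counted on it. The illustrated competing risk belongs to the any-AE curve and does not cover a death after a grade 1 or 2 AE. Beyond that, the handling is unspecified, not wrong.

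The size rests on 107 patients per arm, the assumed event counts, and fatal AEs that follow a low-grade AE. That few such deaths will occur is a judgement; the protocol gives no number. The consequence is minor: one descriptive curve is affected, and no hypothesis test, sample size or decision rule depends on it.

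**What to change.** In section 16.7, Safety endpoints, define the event of the second curve as the first AE of grade 3 or higher. State a competing risk for each curve: keep the present example for the any-AE curve, and for the severe-AE curve use death without a prior or concurrent AE of grade 3 or higher. If a curve of non-fatal severe toxicity is what was meant, say so and label it that way.

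The cost is a few words. Data collection, sample size and the confirmatory tests are unchanged, since AE grade and fatal outcome are already recorded.
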